### Randomization {16a} {16b} {16c}

Randomization will be carried out using a simple randomization based on an equiprobable algorithm. According to randomization algorithm, a three-digit numerical code list will be generated with the R statistical software. It contains the three-digit and the assignation group. This list will be given to the laboratory and to the pharmacy service of the DUH, so only these both will know which of the groups is placebo and which of the groups is experimental. Only the part of the lists containing the 70 three-digit numerical code (not the assignation group) will be given to the main investigator. For each recruited patient, the main investigator will assign consecutively a three-digit code number and give to the patient a document with his name and the three-digit numerical code. When the patient will go to the laboratory, it will know if the patient belongs to the experimental group or the placebo group and proceed to prepare the samples. The principal investigator and the patients will be blinded for the remaining.

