### Data collection {18a} {18b} {19} {27}

At baseline, patient demographics and prior failed therapies will be documented, including frequency, duration, type, and compliance, as well as magnetic resonance imagining (MRI) and electromyography (EMG) diagnostic tests. Documentation of analgesic use for the treatment of LLR will include frequency, dosage, and duration. All baseline and post-procedural follow-up points will include reported outcomes documented through completing the NPRS, ODS, MOAS, SF-12, and DN4 questionnaires and documentation of narcotic and non-narcotic analgesic medication usage. Device and procedure-related adverse events and all serious adverse events will be documented throughout the study period (Table 3).

The data collected will be stored in locked cabinets, and only the main researcher will have access to this information. Data will be recruited in a computer spreadsheet with password protection to ensure confidentiality. To ensure no error, the spreadsheet will be monthly monitored and audited by a researcher who is blind to the participants’ group allocation and has no conflict of interest.

All patients who leave the study for any reason will no longer have their data collected.

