### Monitoring, safety, and quality control

The primary safety endpoint is the incidence of device- and/or procedure-related adverse events, which will be compared statistically between the randomized groups using proportions of patients experiencing such an event. The endpoint will be met if this event rate is not significantly greater with ACS than with PhS. All study-related adverse events will be monitored and reported, including seriousness, severity, treatment, and relationship to the study device/procedure. Adverse events collected in this study will be determined by the mine investigator to be specifically related to the products or procedures used in the 2 treatment groups or one that is determined to be a serious adverse event {22}.

To date, all published studies with ACS have shown high safety rates and no side effects for what ACS product itself represents. Even so, any intervention can lead to an adverse effect, so their monitoring will be an essential condition in this protocol {11b}.

Once the study has started, given that the inclusion of patients will be progressive over time as they are recruited, just in case there is a worsening of pain of more than 25% in more than 50% of the patients, the study would be reconsidered and the recruitment would be stopped to analyze the data and check if the worsening is in patients whom the ACS therapy was applied. If this were the case, the study would be definitively stopped and a report would be given to the laboratory. The author responsible for the study will carry out this audit if necessary. The main investigator together with the rest of the authors will make the decision to terminate the trial early {17b} {21a}.

Any other adverse effect as far as the interventions are concerned will be collected and analyzed (if necessary, the second intervention would be canceled, and the patient would be withdrawn from the study) {11b} {21b}.

The main investigator is the only person who will be in charge of follow-up with clinical interviews at 30 days, 3 months, 6 months, and 12 months. A schedule of visits will be established for each patient for their greater adherence to the study and not to delay follow-up. Apart from the following-up visit controls, the patients will provide from a telephone number of pain unit for any doubts, changing pain characteristics, or new interventions they will receive. In that way, it provides an improving of adherence to protocol of the study {11c}.

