As far as the samples are concerned, both the laboratory responsible for the ACS and the pharmacy of DUH will have a record of the samples and their transport and temperature. Each sample will have a special label (study code, randomization number) and will be guarded by the pharmacy upon arrival from the laboratory and when it is withdrawn by the investigator on the day of its use for injection.

The study will be carried out in the facilities of the DUH, a document of suitability of the facilities signed by the head of the Department of Anaesthesiology and pain unit. In the same way, a commitment document is attached by the Hospital’s Pharmacy Department for the control and monitoring of the study. The main investigator will take the responsibility to monitoring of the study. She will coordinate with the people in the laboratory, pharmacy, and pain unit. There is also a thesis director who will meet monthly with the author responsible for the study and running the trial day-to-day to provide organizational support. In conclusion, since the day-to-day task falls on the main investigator, she will be responsible for any important protocol modification and technical aspects of the trial as well as data collection, outcome analyses, and results. She will be in charge of notifying the rest of authors as well as laboratory and pharmacy {5d} {21a} {25}.

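### The by-arm harm check is given to the author who appears to be the blinded main investigator, sole follow-up interviewer and judge of adverse-event relatedness, with no masked route described

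*Protocol article*

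**What the plan says.** All references are to the protocol article.

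- **Trigger** (Monitoring, safety, and quality control): recruitment is halted and the data examined "just in case there is a worsening of pain of more than 25% in more than 50% of the patients". The count is over all patients, not by arm.
- **Question asked** (same section): the examination is to "check if the worsening is in patients whom the ACS therapy was applied".
- **Consequence** (same section): "If this were the case, the study would be definitively stopped and a report would be given to the laboratory". No consequence is stated for the opposite answer.
- **Who checks and who decides** (same section): "The author responsible for the study will carry out this audit if necessary". The next sentence gives the decision on early termination to the main investigator and the other authors.
- **Blinding** (Randomization): only the laboratory and the pharmacy hold the group assignments. "The principal investigator and the patients will be blinded for the remaining".
- **Follow-up and safety judgement** (Monitoring, safety, and quality control): "The main investigator is the only person who will be in charge of follow-up with clinical interviews". The same section has the investigator determine which adverse events are related to the products or procedures.
- **An existing blinded role** (Data collection): the spreadsheet is checked monthly for errors, "audited by a researcher who is blind to the participants’ group allocation and has no conflict of interest".

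**The concern.** The question put to the checker concerns treatment arm, and the person named to answer it appears to be someone the design needs to keep blind. If she learns allocations and the trial goes on, the double blind is weakened at the point where it depends on her judgement and not on the patient's. The primary safety endpoint is the proportion of patients with a device- or procedure-related event, and relatedness is her call. She may also cancel a second procedure and withdraw a patient because of an adverse effect. Since data collection ends when a patient leaves the study, withdrawals made with knowledge of the arm would remove later pain scores as well.

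**Working it through.** No figure in the plan has to be reproduced. The check traces roles across sections, with a small count to see when the continuing branch can arise and what a by-arm table could reveal.

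**1. Who is the checker?** The monitoring section does not name the main investigator in the audit sentence. It later speaks of "the author responsible for the study and running the trial day-to-day" and then assigns the day-to-day work to the main investigator. The Setting section makes the principal investigator the first person responsible for the project. The identity is therefore an inference, but these statements agree and none points to anyone else.

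**2. Is she meant to be blind?** Yes. The Randomization section says so of the principal investigator. The section on intervention and blinding says the syringes are made identical and sealed so that the main investigator cannot tell the group.

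**3. Does the check expose allocation?** It cannot be answered without allocation in some form. The article does not say whether she would see the list, a table of counts or a masked answer.

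**4. Can the trial continue afterwards?** A definitive stop is tied to worsening in ACS patients, so the other answer implies continuation without stating it. How often that could happen depends on the reading. Assume all 70 patients are assessed, 35 per arm:
- The trigger needs more than 0.5 × 70 = 35 worsened patients, so at least 36.
- At most 35 of these can be on placebo, so at least 36 − 35 = 1 is on ACS.
- If any worsened ACS patient counts as a yes, the answer is always yes and the continuing branch disappears. It returns only if the arms are unequal, which simple randomization and progressive recruitment allow.
- If a yes needs an excess in the ACS arm, an even split of 18 and 18, or any placebo majority, meets the trigger without a stop.

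The text does not say which reading is meant.

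**5. What could a bare count reveal?** She knows which patients worsened. On the same assumption, two splits of 36 bracket the cases without an ACS excess:
- 18 ACS and 18 placebo: the chance that a given worsened patient is on placebo is 18/36 = 50%, so she learns almost nothing.
- 1 ACS and 35 placebo: that chance is 35/36 = 97%, and all 70 − 36 = 34 patients who did not worsen are on ACS (35 − 1 = 34).

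So a by-arm count ranges from harmless to nearly complete unblinding of the patients checked.

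**6. What remains exposed?** NPRS is scheduled after the second intervention, at 30 days and at 3, 6 and 12 months. The second procedure follows the first by 14 days. A patient who contributes a scheduled score has normally had both injections and used at least one of the four visits, leaving at most 4 − 1 = 3. The questionnaires are completed by the patient and transcribed by the investigator.

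**The case against.** The strongest reply is that the article never says she is handed the allocation list. A count by arm would answer the question, the laboratory and pharmacy keep the list, and she already coordinates with both. A reader might infer that following the rule necessarily breaks the double blind. The documents do not support that: they leave the step unprotected, but they do not prescribe unblinding. What remains of the concern is that the audit is assigned to her, no masked route is described, and a count can itself be informative.

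Continuation after the check is also only implied, and under one reading it is rare. That is correct, and it limits how firmly the consequence can be stated.

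A reader might further infer that every later visit and relatedness judgement for all 70 patients would be unblinded, or that second injections would be widely cancelled with knowledge of the arm. Neither follows. The trigger needs post-baseline scores, so visits have already been used. Patients recruited later are not exposed unless the whole list is released. Most patients with scheduled scores have passed the second procedure. Nor does the point show direct bias in the primary pain outcome, which patients score themselves.

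The monthly auditor does not answer the concern. That role is to find spreadsheet errors, and the article gives it no part in the harm check.

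**Conclusion.** The point holds as a conflict of roles that the article itself states, so it is more than a detail left to a fuller document. The by-arm check goes to the person who appears to be the main investigator. She is required to stay blind, is the only follow-up interviewer, and judges the relatedness that defines the primary safety endpoint.

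Its size is limited. It arises only if the trigger is met and the check does not end the trial. It then falls mainly on later relatedness judgements and withdrawal decisions for the patients covered by the check. Efficacy is exposed chiefly through withdrawals, because follow-up data stop there.

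The conclusion rests on three inferences: that the responsible author is the main investigator, that the answer would reach her unmasked or as counts by arm, and that the trial can continue after the check. It is worth correcting because the remedy is simple, not because the trial is shown to be unblinded.

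**What to change.** Reword the audit sentence in the monitoring section:

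1. The blinded monthly auditor, who already works with the spreadsheet, counts the worsened patients.
2. If the trigger is met, the pharmacy, which already holds the list, tabulates those patients by arm.
3. A named person already in the project, with no part in injections, follow-up or adverse-event judgement, reviews the table. The thesis director could serve only if confirmed to have no such involvement; the article mentions only organizational support and monthly meetings.

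Amend the next sentence as well. As it stands, the main investigator and the other authors decide on termination, which would bring the by-arm data back to her. It should say that she, and any author involved in treatment or follow-up, receives only a stop or continue recommendation and no by-arm data.

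The clinical threshold is left unchanged. The cost is protocol wording and confirmation of one reviewer. The small downside is that the main investigator gives up the by-arm view.

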### Sample size {14}

Based on the existing bibliography in relation to the treatment of pain by ACS treatment for other similar affections [32], it is estimated that accepting an alpha risk of 0.05 and a beta risk of 0.2 in a bilateral contrast, 35 subjects in the treatment group and 35 in the placebo group are needed to detect as statistically significant the difference between the proportion of patients with reduction pain of two points on the NPRS scale, which for the intervention group is expected to be 65%, and for the control group, it is expected to be 35%. A rate of loss to follow-up of 10% has been estimated.

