PRF therapy on the DRG has been proposed as a good option for the treatment of persistent radicular pain based on its power of neuromodulation on neuropathic pain [16, 19–30]. It is also minimally invasive, inexpensive, and simple to perform with few complications. The effect of PRF on neuropathic pain resides through different mechanisms, including the generation of heat and an electric field that induces changes in DRG neurons [30]. More than 120 articles dating back 15 years in terms of DRG PRFs are available in the current literature, giving in its best results an improvement of 29.5% at 2 months, and in 13.1% of the patients who improved, this improvement lasted up to 50% still at 12 months [27].

In order to be able to offer effective treatments for LLR, it is necessary open the field of research towards the cellular and molecular changes induced on the DRG. ACS therapy is a conservative treatment based on the patient’s own blood. A simple sample is taken from the patient, incubated and separated using a special device to produce a serum that is high in anti-inflammatory cytokines and growth factors. This serum is injected back into the patient in a series of 2 to 3 doses.

Described in multiple clinical trials, ACS therapy reduces pain and improves function, mobility, and quality of life. Patients are treated safely without too many clinically relevant side effects. None of their rival treatments such as corticosteroid, hyaluronic acid, or platelet recombinant plasma (PRP) are unrivaled in terms of the duration of their effectiveness in reducing pain [31–37]. When studying the pathophysiology at the molecular level, it is estimated that cytokines play a fundamental role in inflammatory processes, in the pathogenesis of joint degeneration, in spinal pathologies, in soft tissue degeneration, and in the immune system, being a factor in this key interleukin-1 [33–35, 38]. If, therefore, all these molecules are used in combination with natural concentration and autologous, better therapeutic effects can be obtained than exogenous drugs.

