## Methods

This is a prospective, double-blind, randomized placebo-controlled trial designed to assess whether therapy with PRF + ACS on the DRG compared to PRF + PhS reduces neuropathic pain and its consequences, in patients with persistent LLR {8}.

In addition, this it to evaluate if the fact of adding ACS can give a greater advantage for the reduction of pain in these patients.

Taking into account that pulsed RDF is currently the interventional treatment with the best results to offer to patients with persistent chronic radiculalgia, it is the design of the study proposed to perform PRF therapy on the DRG for 8 min, 45 V of the root affected to all the patients included in the study. At the end of the PRF therapy, a 3-mL dose of ACS will be administered on the DRG to the patients of the experimental group and a 3-mL dose of 0.9% PhS will be administrated on the DRG to patients of the placebo group.

A schematic patient flow diagram is presented in Fig. 1 as recommended by SPIRIT [39].

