## Discussion

This study intends to adopt a rigorously designed and implemented randomized controlled method to evaluate the efficacy and safety of the administration of PRF therapy, combined with ACS, on the DRG to reduce neuropathic pain in patients with persistent LRP. The aim of this study is to explore a treatment with greater efficacy and fewer side effects for patients with persistent LLR, who have found pharmacologic therapy, corticoid injection therapy, or surgery ineffective. This treatment, if proven effective, may then be used as a complementary treatment to a more persistent pain.

A number of clinical studies show that ACS (Orthokine®) therapy reduces pain and improves function, mobility, and health-related quality of life. Patients can be treated safely and effectively, and no other injection therapy (corticosteroids, hyaluronic acid, PRP) rivals its long-term efficacy in osteoarthritis or musculoskeletal pathologies [31–37]. The use of ACS (Orthokine®) therapy may help to reduce the number of surgeries, the dosage and frequency of pain killing medications, and therefore medical costs in the medium and long term.

To date, only the randomized clinical trial by Becker et al. has shown superiority of ACS over corticosteroids in lumbar radicular pain (3 epidural injections) [32]. Godek et al. in 2016 also proposed a pilot study in which he observed pain improvement in 15 patients who were injected with ACS under ultrasound vision in the foramen affected by lumbar disc herniation [50]. Kumar et al. proposed 20 patients with unilateral lumbar radiculalgia in whom he applied between 1 and 3 injections of ACS in the epidural space; the patients improved their pain at 3 weeks, 3 months, and 6 months, but there was no control group in any of two studies [51].

In all cases, there were no undesirable or secondary effects due to ACS that made the studies reconsider in terms of safety. There is even a randomized pilot study also by Goni in which ACS injections were at cervical epidural level and in which pain improvement was obtained compared to methylprednisolone [52].

The data, daily regular use, and yearlong experience suggest ACS (Orthokine®) serum is an effective and well-tolerated alternative to other injection therapies.

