As Kuffler explains [53], the trigger axon regeneration and Schwann cell proliferation may assist in reducing neuropathic pain. All molecules contained in ACS could give that trigger point. This study aims to highlight the importance of neuromodulation at the molecular level and how treatment with ACS (rich in cytokines, growth factors and especially interleukins) can give a very advantageous synergy to treatment LLR compared to using only corticosteroids or even other platelet-rich plasma serum.

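### At its own rates of 65% vs 35%, 35 per arm gives about 72% power rather than 80%, and the 35% control rate has no documented basis for PRF plus saline

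*Protocol article*

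**What the plan says.** All planning inputs are in the protocol article, section Sample size {14}. The error rates are given as "accepting an alpha risk of 0.05 and a beta risk of 0.2 in a bilateral contrast". The outcome is the proportion of patients with a two-point reduction on the pain scale (NPRS). The expected rate is 65% in the intervention group, and "for the control group, it is expected to be 35" per cent. The section concludes that 35 subjects per group are needed and adds an estimated 10% loss to follow-up. The randomisation section provides 70 codes, so 35 per arm is the number randomised.

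The support offered is "Based on the existing bibliography in relation to the treatment of pain by ACS treatment for other similar affections [32", and no other source is cited there. The Discussion says of the same reference that it "has shown superiority of ACS over corticosteroids in lumbar radicular pain (3 epidural injections) [32".

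The Abstract and Methods define a different comparison. All patients receive PRF on the dorsal root ganglion and are then randomised to ACS or 0.9% saline at the same site.

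**The concern.** There are two problems, and they are separate.

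First, the only cited basis does not match the trial being sized. As the article describes it, reference 32 differs in its control arm (corticosteroid, not PRF plus saline), its experimental arm (ACS with no mention of PRF, not PRF plus ACS) and its injection site (epidural, not the dorsal root ganglion). A control rate for PRF plus saline needs a reason of its own, and the article gives none.

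Second, the sample size does not follow from the stated inputs. If 35 per arm does not deliver 80% power even at 65% vs 35%, the trial carries a larger risk of missing its target effect than the reader is told. A non-significant result would then be judged against the wrong benchmark.

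**Working it through.** **Inputs** (Sample size {14}): p1 = 0.65, p2 = 0.35, difference d = 0.30, two-sided alpha 0.05 (z = 1.960), power 0.80 (z = 0.842), 35 per arm, 10% loss. Allocation is 1:1 (Abstract).

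**Step 1: try to reproduce 35 per arm.** Two-proportion test with pooled variance under the null:

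n = [1.960 × √(2·p̄·(1−p̄)) + 0.842 × √(p1(1−p1) + p2(1−p2))]² / d²

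- p̄ = 0.50, so √(2 × 0.25) = 0.7071, and 1.960 × 0.7071 = 1.386.
- 0.2275 + 0.2275 = 0.455, √0.455 = 0.6745, and 0.842 × 0.6745 = 0.568.
- n = (1.386 + 0.568)² / 0.09 = 42.4, so 43 per arm.
- With 10% loss: 43 / 0.90 = 47.8, so 48 per arm (96 in total).

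Other two-sided versions give 40 (unpooled variance), 43 (arcsine) and 49 (continuity correction), all before loss. None gives 35.

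Two routes come close, and each contradicts the text. A one-sided pooled test gives 34 before loss, but the section specifies a test "in a bilateral contrast" and states a 10% loss. A control rate of 30% gives 31, or 35 after 10% loss, but the stated rate is 35%. The article does not show which route, if either, was used.

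**Step 2: power at the planned size.**

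Power = Φ[(d√n − 1.386) / 0.6745]

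- n = 35: (0.30 × 5.916 − 1.386) / 0.6745 = 0.577, so power is 0.718.
- n = 31.5 (35 × 0.90): (0.30 × 5.612 − 1.386) / 0.6745 = 0.442, so power is 0.671.

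Exact enumeration of the pooled z test at 35 per arm gives 0.699, and Fisher's exact test gives 0.611, so the normal approximation is not understating power. Beta is about 0.28 before loss and 0.33 after it, against the stated 0.2.

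**Step 3: detectable difference.** With 35 per arm, 80% power and a 35% control rate, the same formula gives 32.9 points, about 33, before loss.

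**Step 4: sensitivity to the control rate.** The control rates other than 35% are assumptions, because the article gives no two-point NPRS responder rate for PRF plus saline. With 65% held in the ACS arm:

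| Control rate | Power, 35 per arm | Power, 31.5 per arm | n per arm for 80%, before / after loss |
|---|---|---|---|
| 30% | 85% | 81% | 31 / 35 |
| 35% | 72% | 67% | 43 / 48 |
| 40% | 56% | 51% | 62 / 69 |
| 45% | 39% | 36% | 96 / 107 |

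If the 30-point gain is held instead, with control rates from about 13% to 50%, power at 35 per arm stays between about 72% and 81%.

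**The case against.** The strongest reply is that the section presents the rates as expected values, based on literature for similar conditions, and so discloses an extrapolation. A reader might infer that 65% and 35% were copied from the corticosteroid trial. The documents do not support that: they do not report that trial's responder rates, and the two figures may be the authors' own projection for this design. A condensed article may also leave a fuller justification to the full protocol. This reply stands. What remains is that the one basis the article names has a different comparator.

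A reader might also want to show that 35% is wrong from the article's own statements on PRF. The Introduction reports PRF as "giving in its best results an improvement of 29.5% at 2 months, and in 13.1% of the patients who improved", with that improvement lasting up to 50% at 12 months. Those figures cannot serve as control rates. The 29.5% may be an amount of improvement rather than a share of patients. The 13.1% is worded as a share of those who improved and is tied to a 50% level, not to a two-point reduction. In the other direction, the Methods say that "pulsed RDF is currently the interventional treatment with the best results to offer to patients with persistent chronic radiculalgia", which might suggest a control rate above 35% but gives no figure. The direction of any error is therefore unknown.

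Third, the wide swings in power come from holding the ACS arm at 65%. With the 30-point gain held, power hardly depends on the control rate. This is correct and limits the weight of the control-rate point. It does not help the 80% claim, which fails at 65% vs 35% itself.

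Finally, the Discussion says that ACS "can give a very advantageous synergy to treatment LLR compared to using only corticosteroids or even other platelet-rich plasma serum". A reader might take this as an aim that the design cannot meet. It is commentary: the objectives and the statistical analysis section plan no such comparison, and it has no bearing on the sample size.

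**Conclusion.** The point holds in two limited parts.

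The firm part is arithmetic. At the plan's own rates, 35 per arm gives about 72% power, or about 67% with 31.5 evaluable per arm, against the stated 80%. This assumes a comparison of two proportions, which is how the sample-size section frames the calculation, and that patients lost to follow-up contribute nothing to the 12-month comparison. The planned mixed model could yield somewhat different power, but the section does not use it for sizing.

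The softer part is provenance. The 35% control rate has no documented basis for PRF plus saline, because the only cited source is described as a corticosteroid comparison. Neither the origin of the figure nor the direction or size of any error can be settled from the article. The consequence depends on what is held fixed: from 85% power at a 30% control rate down to 39% at 45% if the ACS arm stays at 65%, but only about 72% to 81% if the 30-point gain is kept.

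**What to change.** Keep 35 per arm and revise Sample size {14} as follows:

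1. Replace the 80% power claim with about 72% at 65% vs 35% (two-sided 5%), falling to about 67% after the stated 10% loss. Alternatively, state a detectable difference of about 33 points at 80% power before loss, at a 35% control rate.
2. State that 35% is an assumption for PRF plus saline, not derived from a PRF comparison, and that reference 32 compared epidural ACS with corticosteroids.
3. Show power over an assumed control range at 35 per arm. With 65% held: about 85% at 30%, 72% at 35%, 56% at 40% and 39% at 45%. With a 30-point gain held: about 72% to 81%.
4. Do not use the Introduction's 29.5% and 13.1% as two-point NPRS responder rates unless their definition is first established from the source.

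This changes wording only and needs no further patients or data, which suits a trial whose recruitment began in February 2022 and was due to finish about February 2024. The cost is that the stated power becomes less favourable, and a non-significant result must be read with that in mind.

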**Methods:**

We plan to conduct a randomized controlled study to compare the efficacy of PRF therapy plus ACS versus PRF therapy plus physiological saline 0.9% (PhS) on the DRG to reduce neuropathic pain in patients with persistent lower limb radiculalgia (LLR) and to contribute to the functional improvement and quality of life of these patients.

Study participants will include patients who meet study the inclusion/exclusion criteria. Eligible patients will be randomized in a 1:1 ratio to one of treatment with PRF plus ACS (experimental group) or PRF plus PhS (placebo group). The study group will consist of 70 patients (35 per group) who have experienced radicular pain symptoms for ≥ 6 months’ duration who have failed to respond to any therapy. Both groups will receive PRF on the DRG treatment before the injection of the sample (control or placebo). Patient assessments will occur at baseline, 1 month, 3 months, 6 months, and 12 months after therapy.

The primary efficacy outcome measure is Numeric Pain Rating Scale (NPRS) responders from baseline to 12 months of follow-up using validated minimal important change (MIC) thresholds. A reduction of ≥ 2 points in NPRS is considered a clinically significant pain relief.

The secondary efficacy outcome measure is the proportion of Oswestry Low Back Pain Disability Scale (ODS) responders from baseline to 12 months of follow-up in the experimental group (PRF plus ACS) versus the placebo group (PRF plus PhS). ODS responders are defined as those patients achieving the validated MIC of ≥ 10-point improvement in ODS from baseline to 12 months of follow-up as a clinically significant efficacy threshold.

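### 35 patients per arm give about 70–75% power, not the stated 80%, for 65% versus 35% responders in a two-sided 5% test, and about 66–71% after the planned 10% loss

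*Protocol article*

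**What the plan says.** The section Sample size {14} gives every input of a two-proportion calculation. Error rates and sidedness are set by "accepting an alpha risk of 0.05 and a beta risk of 0.2 in a bilateral contrast". The outcome is the proportion of patients whose NPRS pain score falls by two points, assumed to be 65% with ACS and 35% with saline. The section then states that "35 subjects in the treatment group and 35 in the placebo group are needed to detect as statistically significant the difference" between these proportions, and adds: "A rate of loss to follow-up of 10% has been estimated". It names no formula and does not say whether the 35 already allows for the loss.

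The rest of the article fixes the total. The Abstract (Methods) says "The study group will consist of 70 patients (35 per group", Study population {10} repeats 70, and the Randomization section provides 70 codes. Nothing is added on top of 35 per arm. The Statistical analysis section sets the significance level at 5%.

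**The concern.** The number of patients and the stated power do not fit together. A 30-point difference centred on 50% is where the binomial variance is largest, and 35 per arm looks too few for 80% power in a two-sided test, even before any loss.

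The stated beta is what a later reader will use to interpret a non-significant result. If the true risk of missing the assumed effect is nearer one in three than one in five, a null finding would be taken as stronger evidence against ACS than the design can supply. The article also presents the trial as a source of level I evidence, so its main design claim should be correct.

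**Working it through.** **Inputs, all from Sample size {14}:** two-sided alpha 0.05 (z = 1.96); beta 0.2 (z = 0.8416); p1 = 0.65; p2 = 0.35; loss 10%. Allocation is 1:1 (Abstract). Derived values: difference 0.30, squared 0.09; p1(1−p1) + p2(1−p2) = 0.2275 + 0.2275 = 0.455; mean proportion 0.5, so 2 × 0.5 × 0.5 = 0.5.

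**1. Trying to reproduce 35 with the stated two-sided test**

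- Unpooled variance: n = (1.96 + 0.8416)² × 0.455 / 0.09 = 39.7, so 40 per arm. With loss: 40 / 0.9 = 44.4, so 45.
- Pooled variance: n = (1.96 × √0.5 + 0.8416 × √0.455)² / 0.09 = 42.4, so 43 per arm. With loss: 43 / 0.9 = 47.8, so 48.
- Arcsine: 42.3, so 43 per arm.
- Continuity-corrected: 49 per arm; with loss 55.

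None gives 35. The most lenient is 5 per arm too high before any loss.

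**2. What does come close to 35**

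- One-sided 5%, unpooled: (1.645 + 0.8416)² × 0.455 / 0.09 = 31.3. Dividing by 0.9 gives 34.7, which rounds up to 35. (Rounding to 32 before dividing would give 36.)
- One-sided 5%, pooled or arcsine, no loss: 33.3, so 34.

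A one-sided calculation is therefore a plausible origin. This is an inference, since the article names no formula.

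**3. Power of the size actually chosen (two-sided 5%)**

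- Pooled: power = Φ[(0.30 − 1.96 × √(0.5/n)) / √(0.455/n)]. At n = 35: (0.30 − 0.2343) / 0.1140 = 0.577, so 71.8%.
- Unpooled: power = Φ[0.30 / √(0.455/n) − 1.96]. At n = 35: 2.631 − 1.960 = 0.671, so 74.9%.
- Exact: binomial enumeration of the rejection region.

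A 10% loss leaves 35 × 0.9 = 31.5 per arm, that is 31 or 32 whole patients.

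| Method | n = 35 | n = 32 | n = 31 |
|---|---|---|---|
| Pooled normal | 71.8% | 67.8% | 66.3% |
| Arcsine | 72.2% | 68.4% | 67.0% |
| Unpooled normal | 74.9% | 71.1% | 69.7% |
| Exact, uncorrected chi-square | 69.9% | 71.2% | 68.8% |
| Exact, Fisher | 61.1% | 61.8% | 58.9% |

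Exact power does not rise smoothly with n, which is why the value at 32 exceeds that at 35. The pooled row is the cleanest for a before-and-after comparison: 71.8% falls to 67.1% at n = 31.5.

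**4. Both readings of the 10%**

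- If 35 already includes the loss, about 31.5 per arm are evaluable and power is 66–71% by the uncorrected methods.
- If 35 is the evaluable number, power is 70–75%, and with 70 enrolled there is no allowance for the expected loss.

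**5. Difference detectable with 80% power** (pooled, proportions symmetric about 50%): 32.9 points at 35 per arm; 34.4 points at 32 and 34.9 points at 31.

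**The case against.** The strongest reply is that the planned test is not a two-proportion comparison. The Statistical analysis section tests the main outcome with a generalized linear mixed model over repeated visits, adjusted for baseline imbalance. Its power cannot be computed from the article. Patients lost late could still contribute their earlier visits, so the after-loss figures are complete-case figures at 12 months, not the exact power of that model. This stands as a limit on what the percentages mean. It does not support 35: the sample size section sizes a difference between two proportions and gives no within-patient correlation or other input that would justify fewer patients. An unstated gain cannot support a stated beta.

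A second reply is that the one-sided origin is unproven and needs a particular combination of variance formula and rounding. That is fair. The mismatch does not depend on it.

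A third is that the 30-point effect is itself an assumption and recruitment was expected to finish around February 2024, so only reporting is affected. This bears on urgency and explains why a wording correction suffices. It does not make the stated figure right.

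**Conclusion.** The sample size statement is wrong as written. For 65% versus 35% in a two-sided 5% comparison of proportions, 35 per arm gives about 70–75% power, and about 66–71% with the 31 to 32 per arm that remain after the plan's own 10% loss. The risk of missing the assumed effect is about 25–30% before loss and 29–34% after it, against the stated 20%. Reaching 80% needs 40 to 43 evaluable, or 45 to 48 enrolled, per arm.

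These ranges cover the uncorrected methods (pooled, unpooled, arcsine, exact chi-square); Fisher's test would give about 61% at 35 per arm. They assume that the quoted responder rates hold and that lost patients add nothing to the 12-month comparison.

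**What to change.** Keep enrolment as it is and correct the paragraph in Sample size {14}, naming one method and using it throughout. Suggested wording, with the pooled normal approximation:

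> With 35 patients per arm, a two-sided 5% comparison of responder proportions has about 72% power for 65% versus 35%, and about 67% if 10% are lost to follow-up. Power of 80% is reached for a difference of about 33 points with 35 evaluable patients per arm, and of about 35 points after the expected loss.

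The paragraph should also say that 35 per arm is the enrolled number, so that the role of the 10% is clear. If another method is preferred, the figures should lie within 70–75% before loss and 66–71% after it.

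The cost is one paragraph and a less favourable stated power. The results paper should quote the corrected figure when interpreting a non-significant result. Keeping the 80% claim instead would mean enrolling 90 (2 × 45, unpooled) to 96 (2 × 48, pooled) patients, which is 20 to 26 more than planned.
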